As a resource considered safe, inexpensive and easy to administer, tDCS could contribute to the rehabilitation of these children, as its neurophysiological effects have been demonstrated to favor the learning of new voluntary motor and postural control strategies. Considering the complexity of brain activity dysfunctions observed in ASD, we need to investigate whether anodal tDCS may (or may not) contribute to motor training results. In addition, it is necessary to understand what are the effects of facilitating cortical excitability of fundamental structures of motor control, such as, for example, the primary motor cortex and the cerebellum. This information may benefit future clinical indications of tDCS for rehabilitation of children with ASD. However, the scientific literature is extremely limited regarding the effects of tDCS on areas of motor control in children with ASD.

The main goal of the present study is to compare the effects of ten 20-min sessions of neurofunctional motor training combined with anodal tDCS over the primary motor cortex, cerebellar region and sham stimulation on motor ability in children with ASD. Specifically, the aim is to determine whether anodal tDCS over these areas of the brain can optimize the effects of gait and postural control training on gross and fine motor skills, mobility, functional balance, motor cortical excitability, cognitive aspects and behavioral aspects in children with ASD. Our central hypothesis is that all individuals will present functional improvements following gait and balance training, but the benefits will be more evident after the administration of active tDCS (primary motor cortex and cerebellar region) compared to the group receiving sham tDCS due to the neurophysiological effects on cortical excitability. Moreover, we believe that the effects of anodal tDCS over the primary motor cortex will be restricted to motor outcomes, whereas the effects of anodal stimulation over the cerebellar region will also be found in outcomes related to cognitive and behavioral aspects.

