### Participants

2.2.

Thirty children will be recruited from the XXX Child Neurorehabilitation Clinic in the city of XXX, XXX. Participants will undergo detailed screening with the eligibility criteria for inclusion in the study.

The sample size was calculated considering the primary clinical results, which are the total and balance score of the Movement Assessment Battery for Children, 2nd ed. (MABC-2) (62). The calculation of the sample size was based on data from a study involving a group of individuals with ASD who received motor training combined with tDCS over the primary motor cortex (59). The estimated effect size of the previous study was 1.39 (change in total MABC-2 score of 16.5 with a standard deviation [SD] of 5.98; change in score of balance category of MABC-2 of 2.4, SD: 1.70; α = 0.05 (two-tailed) and β = 0.8). The estimate indicated a minimum of 24 participants (eight per group). Considering a possible dropout rate of 20%, 30 participants will be recruited.

The children will be screened for participation in the study based on the following:

Inclusion criteria: 1) Diagnosis of ASD confirmed though a clinical examination; 2) Standard neurobehavioral assessment that confirms and categorizes the severity of ASD; 3) Levels I, II and III according to the Diagnostic and Statistical Manual of intellectual disability (DSM-5); 4) Age three to eight years; 5) Sufficient response to understand simple verbal commands; 6) No change in medication in the six months prior to the onset of the study or during the study; 7) Signed statement of informed consent by a legal guardian; 8) Agreement to participate in study through term of assent.

Exclusion criteria: 1) Diagnosis of epilepsy or seizure within the 12 months prior to the onset of the study; 2) Neurological, neuromuscular disorders or syndromes other than ASD; 3) Having been submitted to orthopedic or neurological surgery within 12 months prior to the intervention; 4) Orthopedic deformities with indication for surgery; 5) Implants in the skull or having undergone some neurosurgical procedure; 6) Metallic implants in the head, neck, chest or upper limb; 7) Hearing devices; 8) Degree of cooperation incompatible with the adequate performance of the activities proposed in the present project.

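### Eight children per group falls short of 80% power for the pairwise comparisons the plan names, and the source of the effect size 1.39 is not stated

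*Protocol article*

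**What the plan says.** The calculation is in the protocol article, section 2.2 (Participants). It names two primary scores, MABC-2 total and MABC-2 balance, and takes its data from an earlier study of "a group of individuals with ASD who received motor training combined with tDCS over the primary motor cortex". One effect size is given: "The estimated effect size of the previous study was 1.39". The accompanying inputs are a "change in total MABC-2 score of 16.5 with a standard deviation [SD] of 5.98", a "change in score of balance category of MABC-2 of 2.4, SD: 1.70", and "α = 0.05 (two-tailed) and β = 0.8". The result is stated as "The estimate indicated a minimum of 24 participants (eight per group"), and then "Considering a possible dropout rate of 20%, 30 participants will be recruited". No formula or test is named for the calculation.

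Section 2.5 (Statistical analysis) plans a two-way ANOVA with three groups and four assessment times, followed by Tukey's post hoc test. The Introduction sets the hypothesis as an advantage of active stimulation over sham, while expecting that "all individuals will present functional improvements following gait and balance training".

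**The concern.** Four features of the paragraph raise doubt.

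- The calculation appears to treat the trial as one comparison of two groups. The plan has three groups and a multiplicity-adjusted post hoc test.
- At eight per group a large-sample formula overstates power.
- One effect size stands for two scores whose quoted changes imply very different standardised effects.
- The inputs are described for a tDCS-treated group, with no sham change beside them. If they are before-after changes, they contain the training effect that the plan expects under sham as well.

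What is at stake is how the result will be read. With 24 evaluable children, a non-significant pairwise comparison would be judged against a nominal 80% power that the design does not have. That matters most for motor cortex against cerebellum, because the Discussion hopes the trial will help identify the best target area.

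**Working it through.** **Inputs.** From section 2.2: effect size d = 1.39; two-sided α = 0.05; power 0.80 (assumed to be what β = 0.8 means); n = 8 per group; 20% dropout. From section 2.5: three groups, Tukey. Assumption: 1.39 is a standardised between-group difference in change.

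**1. Reproducing the stated number.** Normal approximation, one unadjusted pair:

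n = 2(1.960 + 0.842)² / 1.39² = 8.12 per group.

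Power at n = 8: Φ(1.39·√(8/2) − 1.960) = Φ(0.820) = 79.4%.

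With d = 2.4/1.70 = 1.41 the same formula gives 7.88, which rounds up to 8 (power 80.6%). For dropout, 24/(1 − 0.20) = 30. So both 24 and 30 reproduce.

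**2. Small-sample t-test, one unadjusted pair.** Noncentrality = d·√(n/2) = 1.39 × 2 = 2.78; df = 14; critical value 2.145. Power = 73.4%. At n = 10 (noncentrality 3.108, df = 18, critical value 2.101) power is 83.6%. At n = 9 it is 79.0%, so ten per group are needed for 80%.

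**3. Tukey, three groups, on change scores.** Critical value = q(0.95; 3, 3(n−1))/√2. At n = 8 this is 3.565/√2 = 2.521 on 21 df, and power = 60.7%. At n = 10 it is 3.506/√2 = 2.479 on 27 df, and power = 73.2%. Eleven per group give 78.1% and twelve give 82.3%.

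**4. Omnibus F-test on change scores.** Noncentrality = n·Σ(μᵢ − μ̄)², in SD units. At n = 8:
- both active groups 1.39 above sham: noncentrality 10.30, power 76.6%;
- one active group at 1.39 and the other halfway: noncentrality 7.73, power 63.4%.

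| Power at d = 1.39 | 8 per group | 10 per group |
|---|---|---|
| Normal approximation, one pair | 79.4% | – |
| Two-sided t-test, one pair | 73.4% | 83.6% |
| Tukey pair, three groups | 60.7% | 73.2% |
| Omnibus F, both active groups at 1.39 | 76.6% | 86.9% |
| Omnibus F, one active group halfway | 63.4% | 75.2% |

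Using d = 1.41 instead moves the n = 8 figures only to 74.7% (t-test) and 62.2% (Tukey).

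**5. Smallest d detectable with 80% power.** Unadjusted t-test: 1.51 at 8 per group and 1.32 at 10. Tukey: 1.70 at 8 and 1.50 at 10.

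**6. Where 1.39 comes from.** Total score: 16.5/5.98 = 2.76, about twice 1.39. Balance: 2.4/1.70 = 1.41. Allowing for rounding of both balance inputs, the ratio lies between 2.35/1.705 = 1.378 and 2.45/1.695 = 1.445, which includes 1.39.

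**7. β.** β is the type II error rate, so β = 0.8 would literally mean 20% power. The number in step 1 is obtained with power 0.80, so this is a slip of notation that leaves n unchanged.

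**The case against.** The strongest defence is that the sample size is not miscalculated. It follows from a recognised formula, and the dropout inflation is right. Sizing on the balance score also takes the smaller of the two quoted effects: if 2.76 were the between-group difference in total score, eight per group would give more than 99% power even under Tukey. Section 2.6 specifies intention-to-treat with values carried forward, so all 30 children may be analysed. At ten per group the unadjusted t-test (84%) and the omnibus test with both active groups at 1.39 (87%) exceed 80%.

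Much of this stands, and it rules out several stronger readings that a reader might infer:

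- *That 1.39 matches neither quoted change.* It agrees with the balance change within rounding. Only the total score fails to match.
- *That 24 is an arithmetic error.* It reproduces. The fault is that the formula does not correspond to the planned comparisons or to samples this small.
- *That the trial's power is 61%.* That figure belongs to a Tukey comparison of one change score. The power of the planned group-by-time ANOVA depends on the within-child correlation and the pattern over four visits, which the article does not give.
- *That 1.39 is certainly a within-group change.* The article does not settle this. It describes a treated group and quotes no sham change, so the fair complaint is that the contrast is unstated.
- *That the trial was planned at 20% power.* The stated number shows otherwise.

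The defence does not rescue the claim at 24 children, where every small-sample calculation above is below 80%, nor the Tukey comparison at 30, which reaches 73%. Section 2.2 also removes children who miss sessions, so it is not assured that all 30 will be analysed.

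**Conclusion.** The concern holds in a limited form. At d = 1.39 and two-sided 5%, eight per group gives 73% power for a single t-test, 61% for a Tukey pair, and 63% to 77% for the omnibus test on change. The 80% implied for 24 children is therefore reached only under a large-sample, unadjusted, two-group formula. With all 30 analysed, the t-test has 84%, the omnibus test 75% to 87%, and the Tukey pair still only 73%.

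These figures assume that 1.39 is a standardised between-group difference in change. If it is a within-group change, the difference from sham could be smaller, since the plan expects sham children to improve too, and power would be lower by an amount the article does not allow one to compute. As an illustration only, an assumed true d of 0.8 would give 32% (t-test) and 20% (Tukey) at eight per group.

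For motor cortex against cerebellum, 80% power under Tukey needs d = 1.70 at eight per group or 1.50 at ten. The article gives no expected difference between the two sites, so that comparison cannot be called powered. The β notation and the unlabelled 1.39 are reporting faults; neither changes the stated sample size.

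**What to change.** Keep 30 children and rewrite the sample-size paragraph:

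- Write power = 0.80 (β = 0.20), and only for a calculation where it holds. Name the formula used.
- State that 1.39 corresponds to the MABC-2 balance score, and whether it is a within-group change or a difference from sham in the earlier study. If it is within-group, say so and do not present it as the expected treatment difference.
- Give power for the Tukey comparison at 24 and at 30 evaluable children (61% and 73% at d = 1.39), labelled as conditional on a change-score model, with the smallest d detectable at 80% power (1.70 and 1.50).
- State that motor cortex versus cerebellum will be estimated with a confidence interval and is not powered, so that a non-significant difference is not read as equivalence.

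The cost is a less favourable stated power. Enrolment, design and analysis do not change. Keeping 80% for a Tukey pair at d = 1.39 would instead take 12 per group: 36 evaluable, or 36/0.8 = 45 recruited. That is a larger change than this point requires.

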**Figure 1 fig1:**
[figure not shown]
List of specific time points on this line. Motor training associated with tDCS (active or sham) at a frequency of five sessions per week for two consecutive weeks (total of ten sessions). MABC-2, Movement Assessment Battery for Children-2; PBS, Pediatric Balance Scale. TUG, Timed Up and Go; ADOS, Autism Diagnostic Observation Schedule; CARS, Childhood Autism Rating Scale.

The study will involve the following visits:

Visit 1: Screening of participants according to the eligibility criteria and signing of the statements of consent.Visits 2 and 3: Initial assessment (pre-intervention) one week prior to the onset of the intervention, with the investigation of motor ability, mobility, functional balance, motor cortical excitability, cognitive aspects and behavioral aspects. After the initial assessment, the participants will be randomly allocated to the different intervention groups. These visits will be held on two non-consecutive days and will last a maximum of 1.5 h.Visits 4 to 14: Ten intervention sessions in accordance with the allocation to the different groups. Sessions will be held for two consecutive weeks at a frequency of five sessions per week (Monday to Friday) with a maximum duration of approximately 45 min, 20 min of which will be tDCS combined with motor training.Visits 15 and 16: Post-intervention assessment one week after the end of the intervention with the investigation of motor ability, mobility, functional balance and motor cortical excitability. These visits will be held on two non-consecutive days and will last a maximum of 1.5 h.Visits 17 and 18: First follow-up assessment four weeks after the end of the intervention, with the investigation of motor ability, mobility, functional balance, motor cortical excitability, cognitive aspects and behavioral aspects. These visits will be held on two non-consecutive days and will last a maximum of 1.5 h.Visits 19 and 20: Second follow-up assessment eight weeks after the end of the intervention, with the investigation of motor ability, mobility, functional balance, motor cortical excitability, cognitive aspects and behavioral aspects. These visits will be held on two non-consecutive days and will last a maximum of 1.5 h

Figure 2 displays the flowchart of the study in accordance with the SPIRIT statement (61).

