Withdrawal criteria: Participants who decline to continue in the study, those not present on the days of the experiment and those who miss up to two of the 10 intervention sessions will be removed from the study.

**Randomization procedure:** Randomization will be performed using a program for the generation of random numbers to allocate the participants to one of the following interventions:Experimental group 1 – Motor cortex stimulation: anodal tDCS over the primary motor cortex combined with neurofunctional motor training;Experimental group 2 – Cerebellar stimulation: anodal tDCS over the cerebellar region combined with neurofunctional motor training;Control group – Sham stimulation: sham tDCS combined with neurofunctional motor training.

Randomization will be performed considering stratification based on the severity of ASD according to the Brazilian version of the Childhood Autism Rating Scale (CARS-BR) (63). The randomization sequence will be generated for each category (mild, moderate and severe) with adequately organized distribution in sequentially numbered opaque envelopes.

**Blinding:** After the inclusion of participants based on the eligibility criteria and after the pre-intervention assessment, the allocation of the participants will be informed to the researcher who will carry out the intervention. The researcher in charge of the randomization process will not participate in any other aspect of the study and will not have access to the participants. The researchers involved in the assessment procedures, the participants and their families will not be aware of the allocation of the participants. This information will be provided to the families and participants after the complete conclusion of the procedures of the study. The investigator in charge of the interventions will not be blinded to the allocation of the participants, as it will be necessary to select the active or sham stimulation option of the equipment.

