### Procedure for handling missing data

2.6.

Statistical analysis will involve intention-to-treat analysis. In the occurrence of missing data during the study, the statistical analysis will be performed by carrying forward data from the previous observation to adjust for the missing data in the assessments after the intervention.

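### Randomised children are removed from the study for absence or missed sessions, which conflicts with the intention-to-treat analysis, and the missed-session rule is defectively worded

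*Protocol article*

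**What the plan says.** - **Withdrawal criteria (section 2.2).** There are three grounds for removal: the family declines to continue, the child is absent on the days of the experiment, or sessions are missed. On the last, "those who miss up to two of the 10 intervention sessions will be removed from the study".
- **Order of events (section 2.1).** "After the initial assessment, the participants will be randomly allocated to the different intervention groups". The ten sessions follow over two weeks. The first assessment after baseline is one week after the intervention ends, with further assessments at four and eight weeks.
- **Analysis (section 2.6).** "Statistical analysis will involve intention-to-treat analysis". Missing values are handled by "carrying forward data from the previous observation to adjust for the missing data in the assessments after the intervention".
- **Sample size (section 2.2).** At least 24 children are needed (eight per group), raised to 30 for a possible 20% dropout.
- **Inclusion criterion 6 (section 2.2).** "No change in medication in the six months prior to the onset of the study or during the study". No consequence is stated for a change after enrolment, and medication change is not among the withdrawal criteria.

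**The concern.** An attendance rule can act only on children who have already been allocated. Intention to treat keeps such children in their assigned group whatever their adherence, and needs their outcomes to be measured where possible. The text speaks of removal from the study, not of stopping the sessions. On its natural reading, follow-up ends too.

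Carrying the previous observation forward keeps the child in the dataset in form only. The plan would create missing outcomes by rule and then fill them with one fixed assumption, that of no change since baseline. Attendance can depend on tolerability, behaviour or early response. If it does, the groups are no longer protected by randomisation on this point, and no later analysis can recover outcomes that were never collected. With eight evaluable children planned per group, each loss counts.

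The rule is also hard to apply as written. The person who delivers the intervention knows the allocation, and the article does not say who decides on removal, so an ambiguous threshold leaves room for uneven application.

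**Working it through.** **1. The plan's own figures.** Section 2.2 gives a two-sided alpha of 0.05, power of 0.80 (printed as beta) and an effect size of 1.39. Its balance figures give 2.4/1.70 = 1.41. By the normal approximation, n per group = 2(1.960 + 0.842)²/d² = 15.70/d².
- d = 1.41: 15.70/1.993 = 7.9, so 8 per group, or 24 in all, as stated.
- d = 1.39: 15.70/1.932 = 8.1, so 9 per group.
- Dropout: 24/(1 − 0.20) = 30, as stated. The allowance is 30 − 24 = 6 children.

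**2. What carrying forward does to a removed child.** Baseline precedes allocation, and the next assessment is one week after the last session. A child removed during the sessions therefore has one observation, the baseline. The values at 1, 4 and 8 weeks become copies of it, so all three change scores are zero.

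If a share q of each group is treated this way, and removal is unrelated to outcome, each group's mean change is multiplied by (1 − q), and so is the difference between groups. If q differs between groups, the difference becomes (1 − q₁)μ₁ − (1 − q₀)μ₀, which can err in either direction.

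**3. How many children the rule would remove.** The session-miss rate p is not in the article. I assume 2%, 5% and 10%, independent misses and no other dropout. The number missed is then Binomial(10, p), and the number removed is Binomial(30, q). Three thresholds are shown because the wording does not settle which is meant. Cells give the share removed and, in brackets, the probability that more than 6 of 30 are removed.

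| Removed if the child misses | p = 2% | p = 5% | p = 10% | p at which expected removal is 20% |
|---|---|---|---|---|
| any session | 18% (0.30) | 40% (0.98) | 65% (>0.99) | 2.2% |
| two or more | 1.6% (<0.001) | 8.6% (0.01) | 26% (0.71) | 8.3% |
| three or more | 0.1% (<0.001) | 1.2% (<0.001) | 7.0% (0.004) | 15.8% |

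Worked case at 5%:
- Any miss: 1 − 0.95¹⁰ = 1 − 0.599 = 0.401, about 12 of 30.
- Two or more: 0.401 − 10(0.05)(0.95⁹) = 0.401 − 0.315 = 0.086, about 2.6 of 30.
- Three or more: 0.086 − 45(0.05²)(0.95⁸) = 0.0861 − 0.0746 = 0.0115, about 0.3 of 30.
- Exactly one or two, the literal text: 0.315 + 0.075 = 0.39. The same quantity is 18% at p = 2% and 58% at p = 10%.

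The first threshold has a closed form: p = 1 − 0.8^(1/10) = 0.022.

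**4. Consequence at 5%.** With any miss counting, about 18 of 30 children (six per group) would have an observed outcome after baseline. By step 2, the difference between groups would shrink to about 0.60 of its value. Under two or more the factor is about 0.91, and under three or more about 0.99.

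**5. Sections side by side.** Section 2.2 inflates the sample as though dropouts leave the analysis. Section 2.6 keeps them in by carrying values forward. The withdrawal rule produces the cases on which the two disagree.

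**The case against.** **The size rests on assumptions.** The miss rate and the independence of misses are not in the article, and the reading of the rule drives the result. If the phrase is a slip for more than two, a 5% miss rate removes 1.2% of children, and the allowance is very unlikely to be exceeded. This stands. A reader might infer that the 20% allowance will be overrun, but the article supports only a conditional statement.

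**The sample does not fall to six per group.** Under the stated carry-forward rule all 30 children stay in the dataset. This stands too. Six per group is the number with observed outcomes at 5% when any miss counts. The harm is imputed no change, not a smaller analysed sample.

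**Medication change.** A reader might infer from criterion 6 that a child whose medication changes is removed. The article does not say so. The defect there is narrower: the condition cannot be checked at enrolment, and its consequence is left open.

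**Removal that differs by arm is not shown.** Families, children and assessors are blinded and the intervention is short. Differential removal is a risk, not an established fact. The conflict with intention to treat does not depend on it.

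**This is a condensed article.** It does not say whether removed children are still assessed, and a full protocol might. But the article states both the removal rule and the analysis principle, and as stated they do not fit together.

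**Conclusion.** The point holds as a conflict between the withdrawal criteria in section 2.2 and the intention-to-treat analysis in section 2.6. Children removed during the intervention would contribute baseline copies at all three later assessments, although they could have been assessed. This assumes only that removal from the study ends assessment, which is its natural meaning.

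The missed-session wording is defective on any reading, because literally it covers one or two misses and leaves out more.

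The numerical size is conditional. With independent misses, expected removals use up the allowance of 6 of 30 at a session-miss rate of about 2.2%, 8.3% or 15.8%, depending on whether one, two or three misses trigger removal. The correction should be made in any case, since it protects the primary comparison and does not depend on which of these rates applies.

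**What to change.** 1. Separate stopping the intervention sessions from leaving the study. Assess every randomised child at the planned 1, 4 and 8 week visits unless consent is withdrawn.
2. State that all randomised children are analysed in their assigned group whatever their attendance. Record sessions attended, and use attendance only to define a secondary per-protocol analysis.
3. Reconcile the missed-session wording so that it states unambiguously which children it covers. The threshold is for the investigators to set. Say who applies it.
4. Reconcile inclusion criterion 6 with the withdrawal criteria and section 2.6. State what follows from a medication change during the study, so that it does not exclude a randomised child from the intention-to-treat analysis.

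The cost is a short amendment. The extra assessments use visits already scheduled. Under this change the attendance rule takes none of the 30 children out of follow-up, so the 20% allowance is kept for true loss to follow-up. Section 2.8 gives January 2023 as the start of recruitment, so any child already removed under the present rule should be counted and reported by group.
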